**Figure 2 f2:**
[figure not shown]
Study design overview for NOURISH-OK Aim 1, which includes a cross-sectional main study and prospective, observational sub-study.

### Main study procedures

#### Recruitment, screening, enrollment, consent and compensation

Our multi-method recruitment strategy will include direct recruitment of Tulsa CARES clients (anticipated reach n=800) through a combination of dear client letters, direct phone calls, and in-person recruitment during Tulsa CARES appointments and sponsored events. Additional dear client letters will be directly mailed by the Oklahoma State Department of Health to individuals participating in the HIV Drug Assistance Program. Indirect recruitment strategies to the broader community of eligible PLWH will include recruitment flyers and business cards at community-based providers, medical clinics serving PLWH, study information booths at community events, and select pharmacies that dispense higher volumes of HIV prescriptions throughout northeastern Oklahoma.

Individuals expressing interest in the study will undergo a telephone or in-person screening interview to confirm eligibility and to discuss study requirements and procedures. Participants will be referred to the study website and encouraged to review its “frequently asked questions” section and informed consent paperwork before their scheduled enrollment appointment. Participants can elect to receive customized appointment reminder texts *via* the HIPAA-compliant Apptoto messaging service and/or phone calls the day before and the day of their scheduled appointment.

The first portion of the appointment will be dedicated to participant completion of study enrollment forms including written informed consent, authorization for use of protected health information in research, and the option to biobank blood samples for use in future studies.

Study compensation was informed through input from PAC stakeholders and will include a $50 gift card from a select list of stores (e.g., Amazon, Wal-Mart, Target), a personalized nutrition assessment results report, and choice of a non-monetary gift valued at $10 (e.g., portable phone battery charger, adult coloring book, paper towel and toilet paper pack). A $15 transportation voucher will additionally be provided to participants living outside of the enrollment site’s county (Tulsa County).

#### Study flow and measures

Study measures will be collected through a combination of interviewer and self-administered surveys, a nutrition and vital signs assessment, and a fasting blood sample. Participants will be encouraged to collect all study measures in a single 2-hour visit. If two sessions are needed, the self-administered survey portion can be completed at a separate appointment within 5 days from the blood sample and nutrition and vital signs assessment. Study measures are summarized in **Tables 1**, **2**.

**Table 1 T1:** NOURISH-OK Aim 1 Study Demographics, Recruitment, and Health Measures.

Variables	Selected Measure
** *Demographics* **	Household size and composition, household income, race/ethnicity, age, sex (biologic variable); sexual orientation (64) and gender identity (65) as recommended by the Fenway Institute.
** *Recruitment strategy* **	Recruitment methods reported by participant including all direct and indirect recruitment strategies
** *Health-related* **	
Heart rate	Digital automatic blood pressure monitor (Medline)
Oxygen saturation	Pulse oximeter (AccuMed)
Blood pressure	Digital automatic blood pressure monitor (Medline)
HIV history	HIV and AIDS diagnosis dates (chart review); Most recent CD4+ and viral load (chart review)
Co-morbidities	**Physical Health Diagnoses:** Self-reported Hepatitis C, Non-alcoholic fatty liver disease, Pre-diabetes, Diabetes, Renal insufficiency or failure, Stroke, Cardiovascular disease, hypertension (adapted from Behavioral Risk Factor Surveillance Survey 2017) (66). **Mental Health:** Depression (Patient Health Questionnaire-9 (PHQ-9)) (67); Anxiety (Generalized Anxiety Disorder-7 (GAD-7)) (68); Cognitive Function 4-item subscale (MOS-HIV) (69) **Chronic Pain:** 2-item subscale (MOS SF-36) (70)
Medications	HIV antiretroviral therapy (ART); insulin secretagogues; insulin; antibiotics; vitamin or mineral supplements (Combination of chart review and self-reported)
Immunization	COVID-19 vaccination status (self-report)
ART adherence	HIV medication adherence (Self-Rating Scale Item (SRSI) (71)

**Table 2 T2:** NOURISH-OK Study Measures.

Variable	Measure(s) or Method(s)
** *Upstream Structural and Social Factors* **	
Adverse childhood events and protective factors	**Childhood emotional, physical, and sexual abuse:** 10-item survey (Adverse Childhood Events (ACE) survey) (20) **Protective Childhood Experiences:** 7-item survey (72)
HIV diagnosis trauma	**HIV diagnosis as a traumatic stressor:** 2-item survey (73)
Current discrimination	**Expanded Everyday Discrimination Scale:** 10-item survey (74)
Food environment	**Perceived local availability and affordability of fruits and vegetables:** 4-item subscale (Nutrition Environment Measures Survey-Perceived (NEMS-P) (75) **Objective local food access:** Presence or absence of food desert using participant home address (USDA Food Access Research Atlas) (76)
Residential environment	**Neighborhood disadvantage:** Calculated to measure contextual effect of place using participant home address; includes income, education, employment, and housing quality domains to estimate degree of neighborhood disadvantage (Area Deprivation Index) (77) **Rurality:** Continuous measure of rurality scaled from 0 (most urban) to 1 (most rural) based on population size and density, % urban residents, and distance to closest metropolitan area (Index of Relative Rurality) (78, 79)
Social support	**Family & friend support for heart healthy eating habits scales (** 80 **):** including 3 of 9 adapted survey items related to healthy eating (81)
** *Food Security* **	
Food security	**Food security:** 10-item measure for high (0 pts), marginal (1-2 pts), low (3-5 pts), very low (6-10 pts) food security (USDA Adult Food Security Survey Module) (63)
Food utilization	**Cooking literacy:** 14-item Cooking Skills Confidence Measure (82) **Food literacy:** 19-item Food Skills Confidence Measure (82)
** *Health Behaviors* **	
Dietary intake	**Dietary quantity:** Absolute and energy-adjusted estimates of energy, macro- and micronutrients, caffeine, and alcohol (Single day 24-hour food recall using ASA24^®^) **Dietary quality:** Inflammatory potential of overall diet (DII^®^/E-DII^®^ using ASA24^®^data) **Skin carotenoid concentration biomarker:** Continuous measure of usual carotenoid and fruit/vegetable intake (Reflections Spectroscopy (RS) Veggie Meter^®^ device) (83) **Mealtime habits:** Meals/day; calories/meal (ASA24^®^); eating meals with others
Sleep quality and quantity	**Sleep quality and quantity:** 3-item measure of sleep duration, latency, and complaints (2007 NHANES National Center for Health Statistics Sleep Disorders survey) (11)
Physical activity	**Physical activity:** 3-item aerobic activity summary index (PA-I) (84) **Sedentary behavior:** 2-item measure to estimate sitting behavior hours per day (adapted from International Sedentary Assessment Tool) (85) **Estimated cardiorespiratory fitness:** Validated gender-specific formula using age, waist circumference, height, weight, resting heart rate, and self-reported physical activity (84, 86)
Tobacco use	**Self-report tobacco use:** 2-item measure for never, ever, or current smoker classification (87); 1-item measure for smokeless tobacco use; 1-item measure for other forms of nicotine **Nicotine dependence:** 2-item measure (88) **Objective first- and second-hand tobacco exposure:** Cotinine (Genway Biotech - Cotinine Direct ELISA) (89)
Alcohol use	**Alcohol use and abuse**: 3-item survey (AUDIT-C) (90) **Alcohol intake past 24-hours:** ASA24^®^ (91)
Substance use	**Substance use:** 2-items from 8-item NIDA-Modified ASSIST Version 2.0 to assess lifetime and past 3 month medical and nonmedical substance use for 9 categories of substances **Medical marijuana card status:** self-report
Chronic stress	**Perceived stress:** 10-item survey (PSS-10) (92) and 1-item COVID-19 pandemic stress (93)
** *Downstream Pathology* **	
Chronic inflammation	**High sensitivity C-reactive protein** (MSD - Vplex CRP Kit)
Body composition and malnutrition risk indicators	**Wrist circumference:** Measured in centimeters using Singer tape measure to estimate body frame size (ADAM Medical Encyclopedia) (94) **Grip strength:** Measured using dynamometer (Jamar) as screening indicator for malnutrition (95) **Waist circumference:** Measured in centimeters (Adapted from NHANES 2019-2020 Procedures) (96) **Segmental BIA:** Fat, lean dry mass, and phase angle estimates for truncal, right arm, left arm, right leg, left leg, total body (RJL Systems Quantum V Segmental BIA) (97) **Height and weight:** SECA stadiometer Model #220, SECA Electronic Scale Model #703 **Body mass index:** kg/m^2^
Glucose homeostasis	**Impaired fasting glucose:** Defined as fasting plasma glucose between 100-125 gm/dL (98) **Fasting glucose** (MyBioSource – Glucose ELISA) **Fasting insulin** (MSD - Vplex insulin Kit) **HgbA1c** (A1cNOW^®^ PTS Diagnostics)
Insulin resistance (primary outcome)	**Insulin resistance:** Quantitative Insulin Sensitivity Check Index “QUICKI” = 1/[log(I_0_) + log(G_0_)], where I_0_ is fasting insulin (microunits per milliliter) and G_0_ is fasting glucose (milligrams per decaliter) (99)

#### Blood sampling, processing, and analysis

Before blood samples are collected, research staff will confirm each participant has fasted a minimum of 10 hours by asking the last time the participant ate or drank anything besides water. Venous blood samples will be collected by a trained phlebotomist using one BD Vacutainer serum tube, one BD Vacutainer EDTA plasma tube, one BD Vacutainer Heparin tube, one BD Vacutainer P800 plasma tube, and one BD Vacutainer CPT tube for peripheral blood mononuclear cells (PBMC). Samples will be transported to the designated study lab and processed within 2 hours of draw according to manufacturer’s instructions. Plasma and serum aliquots will be stored at −80°C until analysis. Peripheral blood mononuclear cells aliquots will be stored for less than 75 hours at −80°C and then transferred to liquid nitrogen vapor phase for cryopreservation until analysis. Laboratory measures, including serum insulin, blood glucose, c-reactive protein, hemoglobin A1c, and blood cotinine, are summarized in **Table 2**.

#### Nutrition and vital signs assessment

Trained research assistants will then conduct a nutrition assessment including height, weight, waist circumference, wrist circumference, grip strength, and a segmental bioelectrical impedance analysis test. Additional vital signs will include resting heart rate, blood oxygen level, and blood pressure. Resting heart rate, waist circumference, gender, and age will be used to estimate cardiorespiratory fitness (84, 86). We will collect one 24-hr food recall using the Automated Self-Administered 24-hour (ASA24^®^) Dietary Assessment Tool as our primary measure of dietary intake from all subjects (91). We will additionally measure skin carotenoid concentration using Reflections Spectroscopy (RS) (83). This will serve as a concentration biomarker to adjust for measurement error in estimated carotenoid and total fruit and vegetable intake from the ASA24^®^-generated dietary intake estimates.

We will measure height and weight (without shoes) to calculate body mass index (BMI) using a medical grade stadiometer and scale. We will measure central adiposity using waist circumference adapted from NHANES guidelines (96). To minimize participant discomfort, participants will identify body landmarks for self-measure in front of a mirror with assistance from staff. We will conduct segmental bioelectrical impedance analysis (BIA) using the Quantum V Segmental BIA (RJL Systems). Participants who may be pregnant or who have implanted electronic devices will be excluded from this measure. Participants with metal surgical implants present on one side of the body will complete a one-sided measure using the side of the body without the implant. Segmental body fat readings (right arm, left arm, right leg, left leg, and torso) will be used to further identify body type pattern associated with insulin resistance (97). We will minimize BIA measurement error associated with dehydration by providing 16 oz. of water 30 minutes prior to measurement. Collectively, these measures will be used to estimate nutritional and functional status.

#### Chart review and surveys

After receiving authorization from participants through the informed consent process, research staff will conduct a medical chart review to obtain participant’s most recent CD4+ T cell and viral load measures and HIV and AIDS diagnosis dates. Alternatively, participants will be required to provide proof of HIV positivity and a copy of their most recent lab work in the past 6-12 months if this information is not accessible *via* chart review. On the day of study enrollment, participants will also be asked to confirm their residential address, demographics, and medication lists from their existing chart records before this information is added to the study database. Residential address will be used to create objective measures of the community environment, including food desert status (100) and residential area socioeconomic deprivation (77).

A 233-item self-administered survey will collect remaining study measures. These measures include early life events, trauma related to HIV diagnosis, perceived availability of food in the participant’s home and neighborhood, nutrition and health behaviors, food and cooking literacy, social support, and emotional, mental, and physical health history.

#### Exit interview and participant follow-up calls

At the end of their study visit, each participant will receive an information packet that includes a list of community resources, including food assistance and mental health services, contact information for study staff, and several study business cards to share with others who may be eligible for the study. Any participant who reported suicidal ideations while completing the PHQ-9 will be connected on-site with a licensed clinical social worker for further evaluation and follow up at this time. Several days after the study appointment, a designated member of the research team will attempt to contact participants *via* phone to collect qualitative feedback for quality improvement purposes. Feedback areas include satisfaction and opportunities for improvement with research staff, study procedures, incentives, and other general feedback.

### Prospective observational sub-study procedures

#### Replicate dietary intake and food security recalls

Upon completion of the cross-sectional study, participants will be randomly selected within their food security group for an invitation to participate in a 4-week observational sub-study. Elucidating the influence of food insecurity on dietary intake presents an important methodologic challenge because intake estimates from those with low and/or very low food security may potentially have higher error as compared to those with high or marginal food security. These differences in error may be due to wider fluctuations in food access throughout each month (101) and seasonally (102) for food insecure groups. Therefore, the primary purpose of the sub-study is to collect replicate dietary recalls to obtain a more precise estimate of usual dietary intake for each food security group, in addition to exploring how food security fluctuates from week-to-week. Trained interviewers will collect replicate dietary recalls and food security surveys *via* phone. At sub-study enrollment, subjects will receive a printed guide illustrating standard food units of measure for reference during phone calls to improve reporting accuracy.

#### Exploratory microbiome measures

Sub-study participants will also be asked to provide a single saliva sample and 4 weekly stool samples for exploratory analyses of microbiome profiles and variables of interest. At the time of sub-study enrollment, participants will provide their saliva sample using a self-sampling saliva test kit (OMNIgene*ORAL, OM-501; DNA Genotek, Ottawa, Ontario, Canada) that allows for DNA stability at room temperature for up to 1 year. Participants will receive four stool collection kits (OMNIgene*Gut, OMR-200.100; DNA Genotek) that will be marked with unique identifiers for self-collection at home. Research staff will instruct study subjects on how to use the kits and store stool samples, which can be kept for up to 60 days at room temperature.

On a randomly-selected day each week, participants will receive a text or phone call notification from research staff requesting to complete their weekly phone survey which includes a 24-hour dietary recall followed by collection of a sample from their next stool. Participants will have the option to return kits by mail or by hand to the enrollment site. Participants will receive up to a $100 gift card upon completion of the sub-study ($25 for each week dietary recall is completed and stool sample is collected).

Upon arrival to the research lab, handling and storage of the saliva and stool samples will follow the manufacturer’s recommendations. For precautionary measures, sample processing and DNA isolation procedures will be under Biosafety Level 2 (BSL-2) containment. Samples will be stored under suitable conditions (long-term storage at -80°C) until processing for DNA isolation. A commercial DNA isolation kit (e.g., Zymo Research ZymoBIOMICS DNA Miniprep Kit) will be used to isolate DNA from saliva and fecal sample aliquots. Isolated DNAs will be quality controlled using spectrophotometry for measurement of DNA concentration and purity (260nm/280nm, 260nm/230nm ratios) as well as agarose gel electrophoresis for determination of DNA integrity. If indicated, isolations will be repeated.

Salivary and fecal DNAs will be processed for 16S ribosomal RNA gene-based analyses of the respective microbiotas. We will target the hypervariable region V4 of 16S rRNA genes using dual-indexed, paired-end amplicon sequencing with an Illumina MiSeq system (Illumina, Inc., San Diego, CA) as described by Kozich et al. (103). The resulting sequence reads will be analyzed following state-of-the-art bioinformatics pipelines for quality control, taxonomic profiling, and differential abundance analyses of microbial communities. Sub-study measures are summarized in **Table 3**.

**Table 3 T3:** NOURISH-OK Aim 1 Sub-study Observational Measures.

	*Sub-Study Enrollment Baseline Measures*
**Gastrointestinal history**	**History of gastrointestinal surgery or health conditions** (self-reported) **Mode of birth (C-section or vaginal delivery)** (self-reported) **Frequency and timing of bowel movements** (self-reported) **Microbiome-altering sexual practices** 12-month history (self-reported)
**Oral health history**	**Oral disease or infection** (self-reported) **Food avoidance due to mouth, teeth, or gums:** 2-item question adapted from (104)
**Medication history**	**Microbiome-altering medications**: 3-month history of antibiotics, antifungals, laxatives, proton pump inhibitors, and probiotics use (self-reported) **Medications taken in the last 12 hours** (self-reported)
**Oral microbiome**	**Most recent consumption of food, drink, caffeine, or tobacco** at time of sample (self-reported) **Self-sampling saliva test** (OMNIgene•ORAL, OM-501; DNA Genotek) **Diversity index:** Alpha and beta diversity analyses **Relative abundance:** Taxonomic analyses
	** *Weekly Measures (4 timepoints)* **
**Dietary intake**	**Dietary quantity:** Absolute and energy-adjusted estimates of energy, macro- and micronutrients, caffeine, and alcohol (Single day 24-hour food recall using ASA24^®^) **Dietary quality:** Inflammatory potential of overall diet (DII^®^/E-DII^®^ using ASA24^®^data)
**Food security**	**Food security in the 30 days:** 10-item USDA Adult Food Security Survey Module (Timepoint 1) (63) **Food security in the past week:** Adapted from previous study to assess daily food security (105) that includes modified HH2, HH4, AD2 measures from 10-item USDA Adult Food Security Survey Module (Timepoints 2 – 4) (63)
**Sleep quantity**	**Sleep quantity:** 1-item measure of sleep duration in the past 24-hours (adapted from 2007 NHANES National Center for Health Statistics Sleep Disorders survey) (11)
**Physical activity**	**Physical activity:** 2-item measure of aerobic activity in the past 24-hours adapted from (84) **Sedentary behavior:** 1-item measure to estimate sedentary behavior minutes in the past 24-hours (adapted from the International Sedentary Assessment Tool) (85)
**Intestinal transit time**	**Self-reported stool sample consistency**: Bristol stool chart (106) **Date and time of most recent bowel movement** at time of dietary food recall (self-report)
**Gut microbiome**	**Self-sampling stool test** (OMNIgene•Gut, OMR-200.100; DNA Genotek) **Diversity indices:** Alpha (e.g., Shannon, Faith’s phylogenetic diversity) and beta diversity analyses **Relative abundance** of specific bacterial groups (e.g., Firmicutes, Bacteroidetes, Proteobacteria, Bacteroides, Prevotella, etc.) **Differential abundance analyses** using participant and dietary metadata
**Medication changes**	Changes in microbiome-altering prescribed and over-the-counter medications reported during Aim 1 enrollment and sub-study participation period

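### Sub-study food security is measured with a 30-day module at timepoint 1 and a past-week measure at timepoints 2 to 4, so only three of the four weekly values are comparable

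*Protocol article*

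**What the plan says.** Table 3 places food security in the block of measures collected at four weekly timepoints, but splits it into two instruments.

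- **Timepoint 1:** the entry is headed "Food security in the 30 days" and uses the 10-item USDA adult module.
- **Timepoints 2 to 4:** the entry is headed "Food security in the past week". It is adapted from an earlier study of daily food security and includes "modified HH2, HH4, AD2 measures from 10-item USDA Adult Food Security Survey Module".

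No past-week item is listed at timepoint 1. The other main weekly rows (dietary recall, sleep, physical activity, stool sample) have no such split.

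The section on replicate dietary intake and food security recalls ranks the aims: "the primary purpose of the sub-study is to collect replicate dietary recalls", "in addition to exploring how food security fluctuates from week-to-week". The abstract's Methods/design paragraph adds that the weekly recalls and stool samples serve to study how food insecurity, diet and the gut microbiome relate over time. The sub-study has 100 participants, 25 in each food security group.

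**The concern.** To describe how a quantity varies from week to week, it has to be measured the same way each week. Here the first of four values differs from the rest in item set and in recall window. A difference between timepoints 1 and 2 therefore cannot be read as change in food security.

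The distortion would probably have a direction. For an item asked in the same words, anything experienced in the past 7 days also falls within the past 30, so the 30-day answer should be affirmed at least as often. If all four values were read as one series, this would tend to show an apparent improvement after timepoint 1. That improvement could be largest in people whose food insecurity comes and goes, who are the people this aim is about. The direction is an inference, because the past-week items are described as modified and their exact wording is not shown.

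The split is fixed at data collection. An analysis plan can choose which timepoints to use, but it cannot recover a past-week answer that was never asked.

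**Working it through.** The article states no precision or power figure for weekly food security, so there is no figure of the plan's own to reproduce. The check is a count, followed by an illustration of precision.

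**Inputs**
- Participants: n = 4 × 25 = 100 (abstract, Methods/design).
- Weekly timepoints: 4 (Table 3).
- Timepoints with the past-week measure: 3, namely 2, 3 and 4 (Table 3).

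**Comparison of the two instruments (Table 3)**

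| | Timepoint 1 | Timepoints 2 to 4 |
|---|---|---|
| Recall window | 30 days | past week |
| Items | full 10-item module | adapted measure including modified HH2, HH4, AD2 |

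Taking only HH2, HH4 and AD2 from the timepoint 1 module would align the item content. The recall window and the modified wording would still differ.

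**Like-for-like counts, complete data assumed**

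| | As written | Past-week items also at timepoint 1 |
|---|---|---|
| Comparable weekly values per person | 3 | 4 |
| Person-weeks | 100 × 3 = 300 | 100 × 4 = 400 |
| Consecutive changes per person | 2 | 3 |
| Within-person degrees of freedom, n(k − 1) | 100 × 2 = 200 | 100 × 3 = 300 |

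**Illustration of precision**

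Assume independent, normally distributed weekly deviations around each person's own mean. The relative standard error of the within-person variance is then √(2 / [n(k − 1)]).

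- All 100 participants: √(2/200) = 10.0% with three weeks; √(2/300) = 8.2% with four.
- One group of 25: √(2/50) = 20.0% with three weeks; √(2/75) = 16.3% with four.
- Ratio of four weeks to three: √(200/300) = 0.816, a standard error about 18% smaller. Equivalently, √(300/200) = 1.225, so the standard error as written is about 22% larger.

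The same ratio applies to the standard error of a within-person association if the weekly exposure has equal, independent within-person variance.

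**The case against.** The strongest reply is that little in the plan depends on this.

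- **Secondary aim.** Weekly fluctuation is an exploratory addition to the replicate recalls, and the microbiome work is also labelled exploratory. This stands and sets the weight of the point.
- **No faulty analysis is planned.** The statistical analysis section specifies no model of weekly food security. It uses food security level to examine dietary measurement error, and it takes variance estimates and intraclass correlations from the repeated microbiome and recall data. A reader might infer that the four values will be run together as one series, but the article does not say so. How the instruments are scored may properly be left to a document not shown. This also stands, though it does not supply the missing past-week answer.
- **A quarter of the data is not lost.** A reader might infer that the first recall and stool sample become unusable. They do not. Past-week values at timepoints 2, 3 and 4 roughly cover the three intervals between successive calls (only roughly, because the call day is random within each week). Diet and stool are collected at both ends of each interval, so food security over an interval can be related to change in diet or stool for three intervals per person, with timepoint 1 as baseline. The loss is confined to matching at the same timepoint and to consecutive changes in food security itself.
- **Number of items.** The past-week measure is said to include three named items. Three is the natural reading but is not stated to be the full set. The difference in recall window holds either way.
- **Overlap with the main study.** A reader might suppose that the 30-day window at timepoint 1 reaches back over the main-study assessment. The article gives neither the interval between the two nor a reference period for the main-study module, so this cannot be derived.

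**Conclusion.** The point holds as a minor one. For describing weekly fluctuation in food security and its relations over time with diet and microbiome, 3 of 4 weekly values and 2 of 3 consecutive changes per person are like-for-like. The step from timepoint 1 to 2 confounds real change with a change of instrument. This follows directly from Table 3 and needs no assumption.

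The gain of about 18% in standard error is only illustrative. It assumes complete data on 100 participants and independent weekly deviations, and it belongs to a within-person analysis that the article does not specify.

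The finding does not extend to the sub-study's main purpose. The dietary recalls and stool samples are collected at all four timepoints and are unaffected. Timepoint 1 food security keeps its value as a baseline severity measure or covariate.

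**What to change.** Ask at timepoint 1 the same past-week items used at timepoints 2 to 4, and keep the 30-day module there as the baseline severity measure. State that week-to-week analyses use the past-week measure only. For participants already past timepoint 1, restrict those analyses to timepoints 2 to 4.

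The cost is a few extra questions in one phone call that is already scheduled, and a minor survey amendment. No visit, sample or eligibility rule changes.
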